#### *Secondary Non-Inferiority Analysis*

Secondary analyses will include assessment of seroconversion in the ITT population as a whole, on the subset of the ITT population with baseline seropositivity to YF, and in the subset of the PP population with no reported history of flavivirus infection. Geometric mean PRNT50 titre (GMT) and GMT fold increase (GMFI) and corresponding 95% confidence intervals (CI) on day 0 and 28 will be calculated. Non-inferiority will be calculated by the difference in GMT and GMFI between the full dose and each lower dose group. Titres will be graphically represented by reverse cumulative distributions obtained by plotting, for each possible value of the titre (abscissa), the proportion of subjects with a titre greater than this value.

Lower vaccine doses may change the kinetics of antibody response. The assessment of seroconversion rates, GMT, and GMFI 10 days after vaccination in the ITT population will provide important information in the context of low dose vaccine usage in outbreak response. These three immunogenicity outcomes will also be assessed at 1 year and 2 years post-vaccination in the ITT population to confirm a lasting effect of full and low dose vaccination.

Relationships between seroconversion and vaccine immunogenicity (PRNT50 GMT and GMFI) will be related to frequencies of specific T and B cell subsets measured by flow cytometry, chemokine and cytokine levels in sera and neutralising antibody levels to other flaviviruses. Correlations between vaccine viraemia and immunogenicity will be assessed across the different vaccine dose strata. Comparisons of immune and viraemia kinetics will be made between the adult and children trial participants using non-parametric tests, whilst accounting for the administered vaccine dose.

Adverse events occurring during the study follow up period will be analyzed and compared between groups. This will be a descriptive analysis and will include all AEs up to 28 days post-vaccination, and SAEs that occurred any time during study follow-up.

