## **2. Study Objectives**

### **2.1 Primary Objectives**

To determine the lowest dose (1000, 500 and 250 IU/dose) of YF vaccine that is non-inferior to the full standard dose as measured by seroconversion using the PRNT50 assay at 28 days post-vaccination.

Seroconversion is defined as a  $\geq 4$ -fold rise in neutralizing antibody titre between pre-immunization (Day 0) and post-immunization samples. Any patient who appears seronegative (PRNT50 value below the Limit of Quantification, 1:10) will be considered to have a baseline titre of LOQ/2, 1:5.

Noninferiority will be assessed by comparing the lower dose to the full dose of vaccine. Since baseline antibody levels can modulate response to the vaccine, the primary analysis will be based on the per-protocol (PP) population, which must be seronegative to YF at baseline. Secondary analysis of seroconversion at Day 28 will be performed in the intent-to-treat (ITT) population, regardless of baseline YF seropositive, and for the subset of adults which are seropositive to YF at baseline. The primary analysis time point will be when each participant has provided a Day 28 post-vaccination blood sample or has surpassed the window (+/- 3 days) to provide this sample.

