### **3.2 Sample Size and Power Considerations**

This study will be powered to detect non-inferiority of each lower dose of vaccine (1000 IU, 500 IU, 250 IU) compared to the full standard vaccine dose.

For the adult study, assuming a 95% seroconversion rate, 90% power, 2.5% level of significance for a one-sided test and a non-inferiority margin of 10%, which gave a sample size of 100 per arm. The 10% non-inferiority margin was chosen in consideration of the public health consequence of a loss of protection but a potential increase in vaccine dosages in a situation where vaccine stocks are insufficient to respond to an outbreak. The sample size was increased by 20% to account for: i) losses to follow up and, ii) unevaluable participants with a positive serological response for YF virus at baseline. Thus, a total sample size of 480 will be required for the four vaccine dose groups (i.e. full dose, 1000 IU, 500 IU and 250 IU).

For the study in children, we assumed a 90% seroconversion rate (accounting for lower vaccine immunogenicity reported in children [4]), 90% power, 2.5% alpha for a one-sided test and a non-inferiority margin of 10%, which gave a sample size of 190 per arm. This was increased by 10% to account for 5% losses to follow up and 5% unevaluable participants with a positive serological response for YF virus at baseline. This gave a total sample size of 420 (i.e. 210 in the full dose group and 210 in the lower dose group).

Analyses of all other efficacy and safety endpoints are supporting only. Therefore, no significant adjustments will be made for multiple comparisons.

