### 3.4 Selection of lowest non-inferior dose group for sub-study

Following the primary analysis time point, the DSMB will determine whether there is sufficient evidence of efficacy and safety to continue the trial in Cohort(B) and will offer a recommendation on which lowest non-inferior dose group to use in the sub-studies.

First, the DSMB shall assess non-inferiority at Day 28 of seroconversion rates (primary analysis), GMT, and GMFI for each dose groups in the adult PP and ITT populations. Any vaccine dose group (i.e.1000 IU, 500 IU, 250 IU) that is shown to be non-inferior in seroconversion and for which no concerns regarding significant variation are noted on secondary analysis will be considered for use in the sub-studies. If the lower doses are inferior to the full dose of all four vaccines, the sub-studies in populations (B) will not be conducted.

The primary endpoint will be assessed 28 days post-vaccination, but study visits will continue for up to two years after vaccination. Venous blood samples for YF titre quantification by PRNT will be collected at baseline, Viremia visit (2-7 days), 10 days (+/- 1 day), 28 days (+/- 3 days), 1 year (+/- 14 days) and 2 Years (+/- 28 days) after vaccination. PRNT for paired samples will be run at the same time to assure comparability of measurements from samples at baseline, 10 days, 28 days, 365 days and 2 years post-vaccination. The quantification of antibodies will be done at the Institut Pasteur in Dakar, Senegal. PRNT is considered the most sensitive and specific test for quantification of neutralizing antibodies and is the reference method for assessing immune response after vaccination.

*Table 1: Study activities timeline*

| Procedure                                     | Screening
Day -30* | Day 0            | Day 2, 3,
4, 5, 6, 7** | Day 10
(+/- 1 day) | Day 28
(+/- 3 days) | Day 365
(+/-14
days) | Day 730
(+/- 28
days) |
|-----------------------------------------------|-----------------------|------------------|---------------------------|-----------------------|------------------------|----------------------------|-----------------------------|
| Informed Consent                              | X                     |                  |                           |                       |                        |                            |                             |

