### 5.3.2 Immunogenicity Analysis

All immunogenicity analyses will be pairwise comparisons of study arms (full vs lower dose group) within each cohort, and only a single lower dose vaccine group will be used for the sub-study in children.

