#### *Primary Non-Inferiority Analysis*

The proportion of subjects who seroconvert will be presented by study arm for each study cohort, along with 95% confidence intervals. The primary analysis will be a pairwise statistical comparison of the rate of seroconversion at day 28 between full dose and each lower dose of vaccine using a non-inferiority test with a margin of non-inferiority of 10% in the PP population. Each immunogenicity assessment will be a pairwise comparison of the full dose and each lower dose within one study population (i.e. adults or children) using Dunnett's Test.

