#### *Pre-existing immunity interference*

We will perform a logistic regression to evaluate the impact of vaccine dose group and pre-existing immunity to YF on rate of seroconversion at Day 28. A logistic regression analysis will be conducted within each study cohort, with adjustment for age at randomization, site, sex, and baseline YF titre (as a continuous variable) and vaccine dose group as covariates. This analysis will be conducted in the subset of the ITT population which is seropositive to YF at baseline (ITT YF+) for each study cohort.

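### The Day 28 whole-ITT comparisons shown to the DSMB include baseline seropositives but do not adjust for the measured baseline YF titre, so they are valid but less precise than they could be

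*Supplement*

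**What the plan says.** - **Baseline antibody matters.** SAP 2.1 explains the restriction of the primary analysis to seronegatives: "Since baseline antibody levels can modulate response to the vaccine".
- **Seropositives are enrolled and enter ITT.** Protocol 8.2.1 says that baseline YF antibody will be used in analysis but is not an exclusion. SAP 3.5 defines ITT as everyone vaccinated with at least one later blood sample, whatever the baseline serostatus.
- **The ITT contrast has no baseline term.** SAP 5.3.2 opens with: "All immunogenicity analyses will be pairwise comparisons of study arms". The primary comparison is made "using a non-inferiority test with a margin of non-inferiority of 10% in the PP population", and Dunnett's test is named. For the secondary set the plan says: "Secondary analyses will include assessment of seroconversion in the ITT population as a whole". No covariate or stratum is named.
- **Baseline titre is a covariate in one model only.** The logistic regression under Pre-existing immunity interference has "baseline YF titre (as a continuous variable) and vaccine dose group as covariates", with age, site and sex. It is confined to the baseline-seropositive ITT subset.
- **The DSMB sees the ITT results.** SAP 3.4 has it assess non-inferiority at Day 28 of seroconversion, "GMT, and GMFI for each dose groups in the adult PP and ITT populations". A dose is then considered for infants if it is non-inferior in seroconversion and secondary analysis raises no concern about significant variation.

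**The concern.** Seroconversion is a 4-fold rise. A seronegative adult is assigned 1:5 and needs a titre of 20. An adult at 1:80 needs 1:320. Serostatus should therefore predict the endpoint strongly. Randomisation is not stratified by it, and SAP 3.4 has paired samples assayed together, so serostatus is not known at enrolment.

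In the PP set every baseline is 1:5 and there is nothing to adjust. In the whole ITT set the mix of seropositives adds variance to the dose contrast. An arm that by chance holds more seropositives looks worse on seroconversion with no dose effect. An ITT limit that misses 10 points while PP meets them could be read as a concern under SAP 3.4 when it reflects only baseline mix.

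**Working it through.** **The plan's own figure.** SAP 3.2 gives, for adults, "assuming a 95% seroconversion rate, 90% power, 2.5% level of significance for a one-sided test" and a 10-point margin, "which gave a sample size of 100 per arm". With n = (1.96 + 1.2816)² × 2 × 0.95 × 0.05 / 0.10², the result is 99.8, so 100. For children at 90%, the same formula gives 189.1, so 190. Both reproduce.

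**Inputs from the plan.** 95% seroconversion in seronegatives, equal in both arms; 10-point margin; one-sided 2.5%; 120 randomised per arm, of which 20 allow for losses and baseline seropositives together.

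**Assumptions, not in the plan for adults.** 5% lost by Day 28, so n = 120 × 0.95 = 114. Seropositive share s, and proportion q of seropositives with a 4-fold rise. With 6 lost, the allowance leaves 14 seropositives, so s is at most 14/114 = 12%.

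**Formulas.**
- Overall rate: P = (1 − s) × 0.95 + s × q
- Unadjusted variance: V₀ = P(1 − P)
- Variance stratified by serostatus: V₁ = (1 − s) × 0.0475 + s × q(1 − q)
- Power = Φ(0.10 / √(2V/114) − 1.96)

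**Worked case, s = 10%, q = 30%.** P = 0.855 + 0.030 = 0.885.
- V₀ = 0.885 × 0.115 = 0.1018; standard error 0.0423; power 65.8%.
- V₁ = 0.04275 + 0.0210 = 0.0638; standard error 0.0334; power 84.9%.

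Simulation (40,000 trials) of the plain difference against a Mantel-Haenszel risk difference gives 65.2% and 84.7%.

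**Power at 114 per arm, unadjusted > stratified (loss in points)**

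| s | q = 20% | q = 30% | q = 50% | q = 70% |
|---|---|---|---|---|
| 2% | 86.5 > 92.3 (5.8) | 87.4 > 91.8 (4.4) | 89.3 > 91.4 (2.1) | 91.2 > 91.8 (0.6) |
| 5% | 76.2 > 90.6 (14.4) | 78.4 > 89.3 (10.9) | 82.9 > 88.2 (5.3) | 87.7 > 89.3 (1.6) |
| 10% | 62.7 > 87.6 (24.9) | 65.8 > 84.9 (19.1) | 73.1 > 82.7 (9.6) | 81.8 > 84.9 (3.1) |
| 12% | 58.5 > 86.4 (27.8) | 61.8 > 83.1 (21.3) | 69.6 > 80.4 (10.8) | 79.5 > 83.1 (3.6) |

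The table uses 1.96. With a Dunnett critical value of about 2.35 for three comparisons, the worked case becomes 51% against 74%: lower power, similar loss.

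**Chance imbalance.** The SD of the between-arm difference in seropositive share is √(2s(1 − s)/114), which is 4.0 points at s = 10%. Multiplied by 0.95 − 0.30 = 0.65, it adds an SD of 2.6 points to the unadjusted difference, against a 10-point margin.

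**Children.** The plan allows 5% seropositive and 5% lost, so n is about 200. With 90% in seronegatives and q = 30% (assumed), V₀ = 0.1131 and V₁ = 0.0960. Power is 84.5% against 89.8%, a loss of 5.3 points.

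**GMT and GMFI.** The SAP gives no margin and no SD, so no power can be computed.

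**The case against.** The case for leaving the plan alone is substantial, and most of it stands.

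- **The contrast is valid.** Chance imbalance adds variance over repeated randomisation, not bias.
- **The size is not known.** Neither s nor q is given for adults. A reader might take a large power loss as a property of this trial; the documents do not support that. Nor does a 15% seropositive share fit at 114 per arm: about 17 seropositives plus 6 losses is 23, against an allowance of 20.
- **The effect on the infant decision is limited.** A reader might infer that the dose choice rests on an underpowered test. It does not. SAP 3.4 puts seroconversion first as the primary analysis, which is PP and wholly seronegative. ITT is a supportive screen with no pass/fail rule, and the sample size was set for the evaluable set. The children's ITT tables come after the decision.
- **Serostatus is partly visible already.** PP is the seronegative stratum, and the seropositive ITT subset has its own tables. SAP 5.3.1 describes pre-existing YF antibody by arm and has the importance of any imbalance noted.
- **Baseline is not wholly absent for titres.** GMFI is a change from baseline, and SAP 4.1.2 words the GMT test as a change to Day 28. Under that wording the two contrasts coincide. SAP 5.3.2 words GMT as a simple difference between arms, under which they can diverge.

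What remains is that no whole-ITT comparison uses baseline as a stratum or covariate. The separate tables let the DSMB suspect a serostatus effect but give no adjusted ITT limit. The only adjusted model is in another population and not on the risk-difference scale.

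**Conclusion.** The point holds as a minor, nearly free improvement in precision. The Day 28 whole-ITT seroconversion comparison omits a measured baseline variable that the SAP itself regards as affecting response. For adults the loss is about 5 to 28 points of power, conditional on 5-12% seropositive, 20-50% of them rising 4-fold, 114 per arm and a 1.96 critical value. It is under 5 points if about 2% or fewer are seropositive (with at least 30% rising) or if 70% or more rise. For children it is about 5 points at the plan's 5% share and an assumed 30% rising. These figures apply to ITT seroconversion only. The primary PP result, and so the main criterion for the infant dose, is untouched.

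**What to change.** In SAP 5.3.2, under Secondary Non-Inferiority Analysis:

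1. Report the ITT Day 28 seroconversion risk difference stratified by, or standardised over, baseline serostatus (PRNT50 below 1:10 against 1:10 or above), for example Mantel-Haenszel, with its confidence interval set against the 10-point margin. The risk difference is collapsible, so standardising over the ITT serostatus mix leaves the estimand unchanged.
2. Use a score-type stratified interval, because the seropositive stratum is sparse. A stratified Wald limit had a simulated one-sided error of about 3.0%, against 2.5-2.8% unadjusted. The power of the score-type interval has not been calculated here and may be slightly below the figures above.
3. Analyse ITT log10 Day 28 titre by ANCOVA on dose arm and log10 baseline titre. The arm coefficient is the same whether the outcome is titre or fold rise, so GMT and GMFI share one between-dose ratio.
4. Keep the unadjusted figures as descriptive.

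The cost is a few lines of text and standard Stata commands. No new data are needed, and the primary analysis does not change.

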Processing of blood will be done within 24 hours of sample collection at the KEMRI CGMRC immunology lab and at the Epicentre laboratory in Mbarara. Samples will be stored at the KEMRI CGMRC and Epicentre Mbarara repositories. The PRNT50 assay for yellow fever will be conducted at the WHO approved reference laboratory at Institut Pasteur de Dakar in Senegal using standard techniques. The lab is performing the PRNT50 assays for the ongoing trial (Clinicaltrials.gov number: NCT02991495) thus allowing comparability of the data generated in this study with that from the ongoing trial using a single PRNT50 assay.

Institut Pasteur de Dakar in Senegal will also be providing the vaccine. However, there will be no conflict of interest, as the vaccine production unit will supply the vaccine while the lab unit will conduct the PRNT50 assays, which are two separate entities. Moreover, the lab personnel will be blinded to the vaccine dose allocations.

High seroprevalence of antibodies to flaviviruses (e.g. dengue virus) has been reported in East Africa [23, 24] raising the question whether presence of antibodies to other flaviviruses at the time of immunization has an impact of YF vaccine immunogenicity. Baseline samples will therefore be evaluated for presence of antibodies to other flaviviruses (including dengue, West Nile and Zika virus) and their association with YF vaccine immunogenicity assessed. The influence of exposure to these related flaviviruses and other locally circulating viruses (e.g. SARS-CoV-2, chikungunya and others) on the magnitude and longevity of the immune response will also be assessed.

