### **2.2 Secondary Objectives**

There are multiple secondary objectives to assess non-inferiority, safety, and immunogenicity in specific populations. These are:

- To describe the geometric mean PRNT50 titre (GMT) at 10 days, 28 days, 1 year and at 2 years post-vaccination of the different doses of the YF vaccine.
- To describe the change in PRNT50 titre (i.e. the geometric mean fold increase (GMFI) as a continuous variable) between baseline and day 28 after vaccination with the different doses of the YF vaccine.
- To measure neutralizing antibody to other flaviviruses (including dengue, West Nile and Zika viruses) on the baseline sample and determine the impact of these antibodies on YF vaccine immunogenicity.
- To assess post-vaccination control of viremia by vaccine dose on samples collected at baseline, and on days 2, 3, 4, 5, 6, 7 and 10 after vaccination.
- To determine the change in T and B cell immune responses between baseline and days 10 and 28 post-vaccination.
- To determine the change in serum cytokine and chemokine levels between baseline and days 2, 3, 4, 5, 6, 7, 10 and 28 post-vaccination.
- To assess the occurrence of adverse events (AE) over 28 days after vaccination and serious adverse events throughout the duration of the study.
- Map out key stakeholders' priorities and perceptions regarding a change in policy towards the use of lower doses of YF vaccine and their potential influence on policy process.

Once results for the main outcome are obtained, data will be reviewed by the study DSMB. The DSMB will then decide if the study should proceed to the second phase where the lowest non-inferior dose, as measured at day 28 in the adult study, will be selected for assessment in children aged 9-12 months co-administered with the Measles vaccine. The aim of these studies will be to: assess the non-inferiority in seroconversion of the lower dose compared to the full standard dose as measured by PRNT50 at 28 days post-vaccination.

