#### **4.1.2 Secondary non-inferiority outcomes**

Geometric mean PRNT50 titre (GMT) on Day 0 and Day 28 will be calculated in the PP population. A test of non-inferiority will be performed for the difference in  $\log_{10}$  GMT from baseline to Day 28 between full-dose and lower dose. Geometric fold increase in PRNT50 titre (GMFI) between Day 0 and Day 28 in the PP population will also be calculated and a similar test of non-inferiority performed. Again, any PRNT50 value reported as below the Limit of Quantification (LOQ) will be converted to a titre of 1:5.

The above non-inferiority assessments of seroconversion, GMT and GMFI at Day 28 will also be assessed in the ITT population, in the subset of the ITT population with pre-existing YF neutralizing antibodies at baseline (ITT FV+), and in the subset of the PP population with no reported history of flavivirus infection (PP FV-).

Lower vaccine doses may change the kinetics of antibody response. The assessment of seroconversion rates, GMT, and GMFI 10 days after vaccination in the ITT population will provide important information in the context of fractional dosing in outbreak response. The three immunogenicity outcomes will also be assessed in 2 years post-vaccination in the ITT population to confirm a lasting effect of full and lower dose vaccination.

Each of the above primary and secondary immunogenicity analyses will be performed in the primary study cohort (A) and replicated in the Children (B) cohort, should the sub-studies proceed.

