#### 4.2.4 Other Assessments

Data on age at randomisation, sex, area of residence, prior flavivirus infection, and body temperature will be collected at the initial eligibility screening and vaccination (Day 0). Pregnancy testing will be required of all female participants at the initial visit. Pregnancy at time of enrolment is an exclusion criterion. HIV testing will be required for participation. Any individual found to be HIV-positive will complete a CD4 count to determine their baseline CD4 level for analysis. As noted above, participants with a verified CD4 count over 200 cells/mm^3 within the last 6 months may be enrolled based on this test, but CD4 count must still be quantified at baseline for use in analysis.

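### The flavivirus-negative per-protocol subset (PP FV-) is defined by reported history although baseline dengue, West Nile and Zika antibodies are measured, and the analysis of those antibodies is not specified

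*Supplement*

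**What the plan says.** **The subset.** SAP 5.3.2 (Secondary Non-Inferiority Analysis) includes an assessment "in the subset of the PP population with no reported history of flavivirus infection". SAP 4.1.2 and protocol 13.2.3 use the same definition. It carries into six table shells: 2.4, 2.17 and 2.30 (adult seroconversion, GMT and GMFI at Day 28) and 2.11, 2.24 and 2.37 (the same for children). The history is recorded alongside the demographic data (SAP 4.2.4): "Data on age at randomisation, sex, area of residence, prior flavivirus infection, and body temperature will be collected at the initial eligibility screening", and again at vaccination.

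**The measurement.** SAP 2.2 lists as a secondary objective "To measure neutralizing antibody to other flaviviruses (including dengue, West Nile and Zika viruses) on the baseline sample and determine the impact of these antibodies"; the response in question is immunogenicity of the yellow fever (YF) vaccine. Protocol 11.2 gives the reason for testing: "High seroprevalence of antibodies to flaviviruses (e.g. dengue virus) has been reported in East Africa".

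**How the measurement is used.** SAP 5.3.2 says that seroconversion, GMT and GMFI will be related to T and B cell subsets, "chemokine and cytokine levels in sera and neutralising antibody levels to other flaviviruses". Protocol 11.2 says that the association of the baseline antibodies with YF immunogenicity will be assessed. Neither gives a model, a cut-off or an analysis population, and SAP section 6 has no table for it.

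**The one specified interference model.** Under Pre-existing immunity interference, SAP 5.3.2 plans a logistic regression of Day 28 seroconversion on dose group and baseline YF titre, adjusted for age, site and sex, in ITT participants who are YF-seropositive at baseline (ITT YF+).

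**The concern.** The trial expects serological exposure to be common and plans to measure it, but it forms its flavivirus-negative group by recall. Anyone infected in the past who does not report it stays in PP FV-. If few participants report a history, PP FV- is close to the whole PP population and each of its tables adds little to the matching PP table.

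A reader of Tables 2.4, 2.17 or 2.30 would take them as the low-dose result in people without prior flavivirus immunity. If a sizeable share are seropositive, the tables do not describe that group, and a difference between naive and exposed participants would be diluted.

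The measured antibodies, which could show such a difference, have a stated purpose but no prespecified analysis. The cut-off and model would then be open to choice after the data are seen.

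**Working it through.** **1. The plan's own sample sizes.** Inputs from SAP 3.2: equal true rates p in both arms, margin 0.10, one-sided alpha 2.5%, power 90%. Formula: n per arm = (1.960 + 1.282)² × 2p(1−p) / 0.10².
- Adults, p = 0.95: 10.51 × 0.095 / 0.01 = 99.8, so 100 (plan: 100).
- Children, p = 0.90: 10.51 × 0.18 / 0.01 = 189.1, so 190 (plan: 190).

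Both reproduce. No size or power is stated for PP FV-.

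**2. Seropositive share of a report-defined subset.** Let s be the flavivirus seroprevalence in PP and r the share of seropositives who report a history. Both are assumptions, because the documents give no figure for either. False reports are taken as zero. The share is s(1−r) / (1−sr), and the fraction of PP kept in the subset is 1−sr.

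| s | r = 0 | r = 10% | r = 50% |
|---|---|---|---|
| 5% | 5.0% | 4.5% | 2.6% |
| 10% | 10.0% | 9.1% | 5.3% |
| 20% | 20.0% | 18.4% | 11.1% |
| 30% | 30.0% | 27.8% | 17.6% |
| 50% | 50.0% | 47.4% | 33.3% |

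The range is about 3% to 50%. At r = 10% and s = 20-30%, PP FV- keeps 97-98% of PP.

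**3. Does the specified interference model cover the PP population?** SAP 3.5 defines PP as YF-seronegative at baseline (PRNT50 below 1:10) and ITT YF+ as 1:10 or above. The two sets cannot overlap. The regression therefore contains no PP participant, and it has no covariate for antibody to other flaviviruses.

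**4. Power if the subset is defined by serology (adults).** Start from 100 PP participants per arm, so n = 100(1−s). Power = Φ(0.10 / √(2 × 0.95 × 0.05 / n) − 1.96).
- s = 0: n = 100, power 90%
- s = 20%: n = 80, power 83%
- s = 30%: n = 70, power 78%
- s = 50%: n = 50, power 63%

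**5. Sparse cells in a dose-by-serostatus model for seroconversion.** At s = 30% there are 30 seropositives per arm. With 95% seroconversion, 30 × 0.05 = 1.5 non-seroconverters are expected per arm. The chance of none is 0.95³⁰ = 21% per arm. The chance that at least one of four arms has none is 1 − (1 − 0.2146)⁴ = 62%. An ordinary logistic interaction model would often be separated.

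**The case against.** - **The objective does not depend on this subset.** A reader might infer that a recall-based subset leaves the cross-reactivity objective unanswerable. The documents do not support this. SAP 2.2 words the objective in terms of measured antibody, and protocol 11.2 and SAP 5.3.2 both relate immunogenicity to measured levels. What remains is that this analysis is unspecified.
- **The size is unknown.** Protocol 11.2 says only that seroprevalence is high in East Africa; it gives no percentage for Kilifi or Mbarara and no reporting rate. That many exposed people will be in the subset is plausible for adults but not certain. Three of the six tables concern infants aged 9-12 months, for whom exposure is less certain and history must come from a caregiver. This stands.
- **The dose comparison is not biased by it.** Reported history is a baseline characteristic, so misclassification does not favour one arm. It changes whom the result describes. This stands.
- **The primary analysis is untouched.** A reader might infer that all six tables repeat it. Only Table 2.4 could nearly do so; the others concern titres, fold rise or children. SAP 3.2 calls the other endpoints supporting. For dose selection, SAP 3.4 names the adult PP and ITT populations, although it also asks in general terms that secondary analysis raise no concern.
- **A serological definition has costs.** It needs a cut-off, shrinks the subset, and makes a binary interaction model fragile (steps 4 and 5). This stands and shapes the fix.

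**Conclusion.** The concern holds in a limited form. PP FV- is formed by report in the SAP, the protocol and six table shells, although a laboratory measure of the same exposure is already planned. In adults the subset is likely to include exposed people and should not be presented as flavivirus-naive. The seropositive share is about 3-50% under assumed seroprevalence of 5-50% and reporting of 0-50%, with no false reports; the documents do not allow a narrower range, and the point is weaker for infants.

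Separately, no subset, model or table uses measured flavivirus serostatus, and the only specified interference regression is confined to people whom PP excludes. The secondary objective on other flaviviruses thus has a stated intent without a prespecified analysis. Neither point affects the primary comparison or the validity of the randomised contrast within the subset.

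**What to change.** Change the SAP (4.1.2, 5.3.2 and the table shells) and protocol 13.2.3 together, since a change to the SAP alone would put the two in conflict.

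1. Define PP FV- as PP participants whose baseline neutralisation results for dengue, West Nile and Zika are all below a stated cut-off, fixed with the laboratory before the results are seen. Keep reported history as a sensitivity definition and label the PP FV- results supportive.
2. Add an analysis in PP of Day 28 log10 titre by baseline flavivirus serostatus, dose group and their interaction, adjusted for site, with a table shell.
3. For seroconversion, present rates with confidence intervals by serostatus and dose, or use a penalised or exact model, because of the sparse cells.
4. Correct the label in SAP 4.1.2 that calls the YF-seropositive ITT subset ITT FV+. SAP 3.5 and 5.3.2 call it ITT YF+, and the slip suggests a serological counterpart to PP FV- that does not exist.

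No new samples or assays are needed. The costs are a protocol edit, a smaller subset with the lower power shown in step 4, and tables that wait for the flavivirus assay and may follow the Day 28 primary report.
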